##### Vaccination status—cross-over

Participants resident in a village allocated to the standard schedule will be defined as cross-over between groups if doses of PCV are received at an age when a dose will function as a booster, as is the intention of the alternative schedule. For infants allocated to the standard schedule, cross-over is defined as administration of (a) two doses of PCV with the second dose administered at ≥252 days (≥36 weeks) of age with an interval of >152 days (>21 weeks), or (b) three doses of PCV with the third dose administered at ≥252 days (≥36 weeks) of age with an interval of >152 days (>21 weeks) between the first and third doses, or (c) four doses of PCV with the fourth dose administered at ≥252 days (≥36 weeks) of age.

The definition of cross-over for infants resident in a village allocated to the alternative schedule is related to receiving three or more doses of PCV at an age when doses will not function as a booster, as is the intention of the standard schedule. For infants allocated to the alternative schedule, cross-over is defined as the administration of (a) three doses of PCV with the administration of the third dose <252 days (<36 weeks) of age, or (b) four doses with the administration of the fourth dose <252 days (<36 weeks) of age. Infants that migrate internally between clusters with alternate group allocation, before completing their PCV schedule, may validly change group allocation to the destination cluster. Internal migrations between clusters with alternate group allocation after completing their PCV schedule will be classified as cross-overs from the time of the migration.

##### Vaccination status—unvaccinated

Children who receive zero doses of PCV will be designated as unvaccinated.

##### Vaccination status—out-migration or death before age to complete vaccination

Vaccination status in individual-level analyses will be defined as out-migration or death before age to complete if the child migrates out at an age before which their PCV schedule could reasonably be completed. Infants resident in standard schedule villages who out-migrate or die before age ≤112 days (16 weeks) and receive zero doses of PCV will be classified as ‘standard schedule, out-migration/death, unvaccinated before age 16 weeks’ and ‘standard schedule, out-migration/death, incomplete before age 16 weeks’ if one or two doses are received. Infants resident in alternative schedule villages who out-migrate or die before age ≤294 days (≤42 weeks) and receive zero doses of PCV will be classified as ‘alternative schedule, out-migration/death, unvaccinated before age 42 weeks’ and ‘alternative schedule, out-migration/death, complete before age 42 weeks’ if one dose of PCV is received.

##### Assessment of individual-level adherence

Individual-level adherence will be assessed as (a) PP vaccination, (b) ITT vaccination, (c) incomplete vaccination, (d) cross-over, (e) unvaccinated, or (f) migration/death before completion. Individual-level adherence will be assessed cumulatively over the 4 years of intervention and reported as proportions of participants enrolled at EPI clinics who fall into these mutually exclusive categories.

##### Assessment of population-level adherence

Population-level adherence to the intervention, or the extent of exposure to the two schedules in the populations of the two groups, will be assessed according to eight mutually exclusive categories (Table 3). Population-level adherence will be assessed by group, on every day of the 4-year intervention period, with all resident children aged 0–260 weeks categorised on each day according to the eight categories. The age at which children are considered eligible refers to the earliest age at which children may have received doses of PCV, taking into account the predominant timing of EPI clinics once per month. That is, the first dose of PCV is scheduled to be given at 6 weeks of age, while the first opportunity to receive the first dose is when the monthly EPI clinic is held and an infant is aged 6 weeks or greater, which may be when the infant is 10 weeks of age. A dose of PCV administered before 6 weeks of age is considered ‘effective’ given the known immune response when PCV is administered in the neonatal period [22, 23].

**Table 3 Tab3:** Population-level adherence to the intervention for resident children aged 0–260 weeks

	Alternative schedule	Standard schedule
Ineligible 0 doses	Age <10 weeks and 0 doses	Age <10 weeks and 0 doses
Eligible 0 doses	Age ≥10 weeks and 0 doses	Age ≥10 weeks and 0 doses
Eligible 1 dose	Age <44 weeks and 1 dose	Age <14 weeks and 1 dose
Eligible 2 doses	Age ≥36 weeks and 2 doses and PCV2 ≥36 weeks	Age <18 weeks and 2 doses
Eligible 3 doses	3 doses and age PCV3 ≥36 weeks	3 doses and age PCV3 <36 weeks
Eligible 4 doses	Enrolled 2 Sept 2019–7 Feb 2020 and 4 doses and age PCV4 ≥36 weeks	4 doses and age PCV4 <36 weeks
Incomplete	Age ≥36 weeks and 1 dose Age <36 weeks and 2 doses Age ≥36 weeks and 2 doses and age PCV2 <36 weeks	Age ≥14 weeks and 1 dose Age ≥18 weeks and 2 doses
Cross-over	3 doses and age PCV3 <36 weeks 4 doses and age PCV4 <36 weeks	3 doses and age PCV3 ≥36 weeks 4 doses and age PCV4 ≥36 weeks

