#### Trial design

Each cluster is randomly allocated, in a 1:1 ratio, to one of two study groups. Infants who have not completed their PCV schedule and are aged <9 months are allocated to receive either the alternative or standard PCV schedule. The alternative schedule specifies eligibility for doses at 6 weeks and 9 months of age. The standard schedule specifies eligibility for doses at 6, 10, and 14 weeks of age. This design permits the estimation of the combined direct and indirect effects at the population-level.

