##### Vaccination status—incomplete vaccination

Incomplete vaccination with the standard schedule will be defined as administration of only one dose of PCV, or administration of two doses of PCV with the second dose administered at ≤252 days (≤36 weeks) of age. Incomplete vaccination with the alternative schedule will be defined as the administration of only one dose of PCV, at any age. For individual-level ITT analyses, children with incomplete vaccination will be assigned to the group to which they were randomised.

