**Non-adherence to vaccine schedule**	
Incorrect dose given	
Standard schedule—received >3 doses	
Standard schedule—3rd dose age >40 weeks	
Alternative schedule—2nd dose age <40 weeks	
Alternative schedule—3rd dose age <40 weeks	
Ineligible and received alternative schedule	Non-resident—2nd dose age ≥36 weeks
Withdrawn and received alternative schedule	Withdrawn—2nd dose age ≥36 weeks

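### Table 3 files the two-dose 1+1 pattern in standard villages under 'Incomplete', although the individual-level rules call it cross-over, so population-level cross-over in the standard arm is understated

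*SAP article*

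**What the plan says.** The schedule under test is a two-dose schedule (Trial design): "The alternative schedule specifies eligibility for doses at 6 weeks and 9 months of age".

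For individual children in standard villages, the section on cross-over includes, as its first pattern, "two doses of PCV with the second dose administered at ≥252 days (≥36 weeks) of age with an interval of >152 days (>21 weeks"; the stated reason is that a dose at that age acts as a booster. The section on incomplete vaccination keeps its own two-dose pattern to an early second dose: "administration of two doses of PCV with the second dose administered at ≤252 days (≤36 weeks) of age".

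Table 3 (Assessment of population-level adherence) sorts all resident children aged 0–260 weeks into eight mutually exclusive categories on every day of the trial. In its standard-schedule column:

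- *Incomplete* is "Age ≥14 weeks and 1 dose Age ≥18 weeks and 2 doses" (two separate lines of the cell).
- *Cross-over* is "3 doses and age PCV3 ≥36 weeks 4 doses and age PCV4 ≥36 weeks" (again two lines).

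Table 3 feeds the daily stacked histogram described under Presentation of adherence among children in resident population. A separate frequency table and histogram for enrolled participants use the individual-level categories.

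**The concern.** The same dose history gets two different labels in one document, and it is the history that matters most in the control arm: the test schedule delivered in a standard village. Table 3 is also uneven between arms. The exact 3+0 pattern in an alternative village falls under *Cross-over*, because three doses with the third before 36 weeks are listed there. The exact 1+1 pattern in a standard village does not.

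Table 3 and its plot are the SAP's measure of how far the two populations were exposed to the two schedules. The primary analysis includes all resident children with clinical pneumonia, enrolled or not, so this plot describes exposure in the population from which they come. In a non-inferiority trial, exposure of the control arm to the test schedule makes the arms more alike, and a reader needs to see how much of it there was. The SAP itself discusses dilution towards the null under Population-level primary endpoint, for alternative villages.

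**Working it through.** No sample-size or power figure is involved, so the check is a comparison of rules.

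**Inputs.**
- Individual cross-over, two-dose rule (standard village): dose 2 at ≥252 days and interval >152 days, taken as the interval between the two doses.
- Individual incomplete (standard village): one dose, or two doses with dose 2 at ≤252 days.
- Table 3 *Incomplete*, standard column, two-dose line: age ≥18 weeks = 18 × 7 = 126 days, with no condition on age at dose 2.
- Table 3 *Eligible 2 doses*, standard column: age <126 days.
- Table 3 *Cross-over*, standard column: three or four doses, last dose at ≥36 weeks = 36 × 7 = 252 days.

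**Step 1: does the conflict always occur?** A child who meets the two-dose cross-over rule is at least 252 days old when dose 2 is given. Since 252 > 126, that child is past the 18-week limit on that day and on every later day. While the child has two doses, the only standard-column category that applies is *Incomplete*.

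**Step 2: worked histories (dose ages in days).**

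| Village | Doses | Individual rule | Table 3 |
|---|---|---|---|
| Standard | 42, 274 (interval 232) | Cross-over | Incomplete, every day from 274 to 1820 |
| Standard | 70, 300 (interval 230) | Cross-over | Incomplete |
| Standard | 42, 70, 274 | Cross-over | Cross-over |
| Standard | 42, 70, 98, 274 | Cross-over | Cross-over |
| Alternative | 42, 70, 98 | Cross-over | Cross-over |

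The two-dose late-booster pattern is where the two sets of rules part.

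**Step 3: grid check.** Dose 1 was taken at 14–199 days (186 values) and dose 2 at 252–729 days (478 values), giving 186 × 478 = 88,908 histories. Those with an interval ≤152 days number 1 + 2 + … + 100 = 5,050, which leaves 83,858 that meet the two-dose rule. Each was classified in Table 3 on the day of dose 2, 100 days later and at 1820 days: 3 × 83,858 = 251,574 checks. All 251,574 gave *Incomplete* and none *Cross-over*.

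**Step 4: effect on the plot.** If a share p of resident children in standard villages has this pattern on a given day, the *Cross-over* band is p too low and the *Incomplete* band p too high. The SAP gives no value for p. For assumed values of 2%, 5% or 10% the shift is 2, 5 or 10 percentage points.

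**The case against.** Much can be said for the plan, and most of it stands.

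- **Cross-over in the standard arm is not reported as zero, nor counted in one arm only.** A reader might infer either from the missing two-dose line. Three- and four-dose children with a last dose at 36 weeks or later are in the standard-column *Cross-over* entry, and a two-dose child who later receives a third dose joins them. The two-dose children are misfiled, not dropped.
- **Enrolled children are covered elsewhere.** Their frequency table and histogram use the individual-level rules and will show two-dose cross-over. They do not cover residents who were never enrolled, so they do not replace Table 3.
- ***Incomplete* is literally true of the allocated schedule.** A two-dose child past 18 weeks has not had three doses. But the SAP's own individual rules keep the late-booster pattern out of incomplete, and the alternative column of the same Table 3 row does condition on age at dose 2.
- **The primary estimate does not move.** It is tempting to translate the misfiling into a prevalence ratio closer to 1. The label cannot do that: children are assigned by village of residence, whatever doses they received. Any real contamination would be in the estimate under either label, and the SAP gives no rate from which to size it.
- **Table 4 is not a further contradiction.** It lists protocol deviations, among them "Standard schedule—3rd dose age >40 weeks", and has no line for a late second dose in the standard arm. Nothing in the SAP calls that a deviation, and infants with an unfinished PCV course could be enrolled up to 274 days of age (182 days in standard villages in the early period). A new row there would be a preference.

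**Conclusion.** The contradiction is real but narrow. Table 3 disagrees with the individual-level rules on cross-over and incomplete vaccination for one pattern: two doses in a standard village, the second at 36 weeks or later with an interval above 152 days. The disagreement holds for every such history. Population-level cross-over in the standard arm is therefore understated in the daily exposure plot, one for one with the share of children who have the pattern. That share cannot be derived from the SAP and may be small.

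The consequence is for the description of adherence and for how contamination is judged when the non-inferiority result is read. No estimate, confidence interval or non-inferiority conclusion changes. The finding rests on reading Table 3 as written.

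A separate, minor wording point sits in the section on out-migration or death before the age to complete vaccination. A one-dose infant who leaves or dies in the alternative arm is labelled "alternative schedule, out-migration/death, complete before age 42 weeks". The section on incomplete vaccination calls one dose of that schedule incomplete at any age, and the list of individual-level categories names this group as migration or death before completion. It reads as a slip and neither supports nor weakens the point about Table 3.

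**What to change.** Reconcile Table 3 with the individual-level cross-over rule, in the standard-schedule column only:

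- *Incomplete*: limit the two-dose line (age ≥18 weeks) to children who do not meet the two-dose cross-over rule.
- *Cross-over*: add a line for two doses with PCV2 at ≥36 weeks and an interval >152 days.

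A child with doses at 42 and 274 days is then a cross-over under both definitions, and the categories remain mutually exclusive. When the text is opened, note that a second dose on exactly day 252 currently satisfies both the individual incomplete limit (≤252) and the cross-over limit (≥252); one of the two should be made strict.

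Separately, reconcile the out-migration/death label for the one-dose child in the alternative arm with the definition of incomplete vaccination.

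The cost is a few words in the SAP and one recoded category. The existing rules already rely on age at each dose, so no new data are needed and no analysis model changes.

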#### Presentation of adherence to the intervention

##### Presentation of adherence among participants enrolled to receive interventions

Adherence among individual enrolled participants will be presented in tabular and graphical forms. A frequency table will show the proportions of all enrolled participants in each group who fall into the mutually exclusive categories of adherence described on p. 12 and 13. A histogram with stacked bars will represent the proportions of all enrolled participants in each group who fall into the categories.

##### Presentation of adherence among children in resident population

Adherence among resident children, or the extent of exposure to the two schedules in the populations resident in the villages allocated to the two groups, will be presented in graphical form. The proportions of resident children aged 0–260 weeks who fall into the mutually exclusive groups defined in Table 3 will be calculated on each day of the 4-year trial period and a histogram plotted with vertically stacked bars to a 100% total for every day over the 4-year period. In order to illustrate the increasing exposure of the population in the alternative schedule villages to the alternative schedule, the plot will demonstrate the increasing proportion over time of resident children who fall into the Table 3 adherence categories of ‘eligible 2 doses’, ‘eligible 3 doses’, and ‘eligible 4 doses’ over the 4-year trial period.

#### Definition of protocol deviations

Table 4 defines the protocol deviations in the trial. Enrolment of ineligible participants occurs when non-residents or infants greater than the age limit are enrolled. Incorrect administration of PCV doses occurs when infants enrolled in the alternative schedule group receive a second or third dose of PCV before 40 weeks of age, and in the standard schedule group if the third dose is administered after 40 weeks of age.

**Table 4 Tab4:** Definition of protocol deviations

**Reason for protocol deviation**	
Enrolment of ineligible participant	Age >40 weeks on day of consent Non-resident on day of consent
Enrolment without consent	Enrolled without valid consent form
**Non-adherence to vaccine schedule**	
Incorrect dose given	
Standard schedule—received >3 doses	
Standard schedule—3rd dose age >40 weeks	
Alternative schedule—2nd dose age <40 weeks	
Alternative schedule—3rd dose age <40 weeks	
Ineligible and received alternative schedule	Non-resident—2nd dose age ≥36 weeks
Withdrawn and received alternative schedule	Withdrawn—2nd dose age ≥36 weeks

#### Which protocol deviations will be summarised

Protocol deviations will be summarised in Table 4.

### Analysis of populations and cohorts

#### Population-level analysis of populations and cohorts

##### Primary endpoint

Estimation of the impact of the schedules in the population incorporates both direct and indirect effects of the schedules in those aged <5 years in the geographic area. Measurement of the primary endpoint in year 4 of intervention allows time for the development of potentially differential impacts of the two schedules. The primary endpoint will be measured in all resident children aged 14–1826 days (2–260 weeks) presenting to health facilities in the study area with clinical pneumonia in year 4, assigning them to each group according to the group allocation of their village of residence, and regardless of whether the child was enrolled as an infant to receive the study intervention or number of PCV doses received (Table 1). Children eligible for selection for measurement of the primary endpoint will be (a) born in the HDSS, (b) resident in the HDSS in year 4, (c) aged 2–260 weeks on the day of presentation, and (d) present with clinical pneumonia at a health facility in the trial area. Neonates aged <14 days are excluded as pneumococcal carriage is low at this age and to avoid potential ascertainment bias due to clinical events in the early neonatal period that are unrelated to pneumococcal transmission. The primary endpoint is a measure of VT prevalence in children with clinical pneumonia and does not require follow-up. VT carriage prevalence in each trial group will be calculated with the denominator being number of children eligible for measurement.

PVS is a pragmatic trial under real-world conditions that aims to compare the impact of the two schedules in the population, taking into account direct and indirect effects. Figure 1 illustrates how coverage of the schedules will change over the 4 years of intervention, and by extension the timeline over which the impact of the schedules will develop. Figure 1A shows the projected coverage of the trial standard schedule (6, 10, 14 weeks) increasing over time (shaded area) in the allocated clusters. The projected coverage of the national standard schedule (2, 3, 4 months) decreases over time. A small proportion of children in the population never attend EPI clinics (~5%) and so maximum coverage is <100%. Figure 1B shows the projected coverage of the alternative schedule (6 weeks, 9 months) increasing over time (shaded area). Children in the population who never attend EPI clinics never receive PCV (~5%) and a proportion of children decline consent for the study and receive the standard schedule (~3%). Figure 1 shows that in year 4, coverage of the alternative schedule will still be increasing and not yet have reached maximal coverage. Figure 1B illustrates that in year 4, children represented by the shaded section will experience the direct and developing indirect effects of the 1+1 schedule, while those represented by the unshaded section will experience the direct effects of the 3+0 schedule and the developing indirect effects of the 1+1 schedule. Thus, in year 4, the majority of alternative schedule children aged 2–260 weeks will be experiencing the direct and indirect effect of the 1+1 schedule but a small proportion will be experiencing a mixture of effects of the standard and alternative schedules.

